#### Intervention study (step 4)

As a secondary objective, inter-group comparative analyses will be performed before and at the end of the intervention on the principal outcome on a small subsample.

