**Methods:**

Our main objective isto evaluate the impact of marketing on a population with an AUD. The methodology was in 4 steps: step 1 is a pre-test (*N* = 100) selecting type of alcohol consumed and type of marketing stimuli identified by patients aged 18 + with an AUD. Step 2 is a qualitative study (*N* = 20), with in-depth interview, to understand links between alcohol marketing and patients with AUD behaviours. Step 3 is a quantitative study(*N* = 600) to confirm these links and the impact of alcohol marketing on patients with AUD behaviours. Step 4 is an interventional step, including and testing the impact of demarketing intervention on patients with AUD while using the results of the three first steps (*N* = 120).

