The intervention will be offered during the inclusion period of 1 year to every drinker with an AUD who seeks treatment in follow-up,as an out-patient, at Brest UniversityHospitaland who fulfils the inclusion criteria and is consulting at Brest UniversityHospital. Intervention will be presented as a series of therapeutic educational group meetings; the objective is to involve drinkers, to help them to make their decisions, and to help them to reduce alcohol consumption risks. Therapeutic educational groups respond perfectly to these criteria [48].

Four sessions will be organised to facilitate participation and limit the number lost to follow-up. Group meetings will be organised every 2 weeks; they will last 2 h; a nurse specialising in addictive disorders and a physician will lead the groups.

After their consent, a randomisationprocedure will select 2 groups to be compared. Participants will be randomized 1:1: control group / intervention group. The Data Management Unit (UGD) of the Brest CHRU will be responsible for the randomization (computer-generated random numbers).

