##### Intervention group

An educational group therapy focusing on damage caused by alcohol, strategies to control alcohol consumption and to reduce alcohol consumption risks. They will be offered in 4 sessions (2 h, twice a month), with the inclusion of a specific session focusing on manipulation of the consumer, marketing strategies and counter-marketing. The session content will be developed according to the results of the qualitative analysis. It will present explanations concerning alcohol marketing strategies and documents regarding alcohol marketing influences. Then participants will be asked to develop cognitive alternatives to identify and fight against the influence of alcohol marketing strategies.

The impact will be analysed to examine thepatients’ perception of their ability to control their alcohol consumption and to control alcohol craving at the end of the group sessions and 3 months later.

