### Statistical analysis

#### Observational study (step 3)

We will first perform a descriptive analysis of the sample. Quantitative variables will be summarised by mean and standard deviation if they are normally distributed; otherwise, by median first and third quartiles. Qualitative data will be summarised by counts and proportions. Comparative multivariate analyses will be performed to determine variables associated with several patient profiles. With a 5% alpha risk and 95% power, to be able to detect small effect sizes in a multivariate analysis (F-squared of 0.05) using 20 parameters a sample size of 600 patients will be necessary.

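### Step 4 describes between-arm comparisons before and at the end of the intervention; stating the effect as the end difference adjusted for the pre-intervention value would gain precision at almost no cost

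*Protocol article*

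**What the plan says.** Step 4 is a two-arm randomised comparison: "Participants will be randomized 1:1: control group / intervention group". The Abstract gives its size as 120. Both arms receive four educational group sessions, and the intervention arm's programme includes one specific session on marketing and counter-marketing.

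The Intervention group section says the impact concerns patients' "perception of their ability to control their alcohol consumption and to control alcohol craving", assessed "at the end of the group sessions and 3 months later". It names no scale and does not mention a measurement before the sessions.

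The only analysis text for this step is a single sentence in the Statistical analysis section, which presents the analysis as secondary and says that "inter-group comparative analyses will be performed before and at the end of the intervention". The variable compared is the main outcome, and the sentence refers to a small part of the sample. It names no test, model, change score or covariate.

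**The concern.** The sentence puts a comparison of the arms before the intervention on the same footing as the comparison at the end. Participants are randomised, so any difference between the arms before treatment is due to chance, and comparing them then gives no information on the intervention. The comparison at the end does address the effect, but nothing in the sentence links it to the earlier value of the same outcome, although the word *before* implies that this value will be available.

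A self-rated measure of control or craving often predicts its own later value. Leaving it out has two consequences. The interval for the effect is wider than it need be, and a chance difference at baseline passes in part into the end difference actually observed. Both matter here because the trial is small and the contrast is narrow: the arms differ by the content of one session within otherwise similar programmes.

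**Working it through.** **Is there a figure to reproduce?** No. The article gives 120 for step 4 without an effect size, standard deviation, power, dropout or correlation. Its only sample size calculation with inputs is for step 3 and does not bear on this point.

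**Inputs.**
- From the article: N = 120 (Abstract) and 1:1 allocation (STEP 4), hence 60 per arm.
- Assumed: all 120 analysed; a continuous outcome with the same standard deviation (SD) in both arms; two-sided 5% level; baseline-to-end correlation r of 0.3, 0.5 or 0.7; for the power figures, a true difference of 0.5 SD.

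**Precision.** With baseline adjustment (analysis of covariance), the variance of the end difference is multiplied by 1 − r². The number of unadjusted patients that gives the same precision is 120/(1 − r²). These are large-sample formulas.

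In SD units, the standard error without adjustment is √(2/60) = 0.183. The difference detectable with 80% power is (1.96 + 0.84) × 0.183 = 0.51 SD; adjustment multiplies it by √(1 − r²). Power for 0.5 SD is Φ(0.5/SE − 1.96), with SE = 0.183 × √(1 − r²).

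| r | 1 − r² | Variance reduction | Equivalent unadjusted N | Detectable difference (80% power) | Power for 0.5 SD |
|---|---|---|---|---|---|
| no adjustment | 1 | – | 120 | 0.51 SD | 78.2% |
| 0.3 | 0.91 | 9% | 132 | 0.49 SD | 81.9% |
| 0.5 | 0.75 | 25% | 160 | 0.44 SD | 88.5% |
| 0.7 | 0.51 | 49% | 235 | 0.37 SD | 97.0% |

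**Chance imbalance.** The between-arm difference in baseline means has a standard error of 0.183 SD, so 95% of randomisations give a difference within ±1.96 × 0.183 = ±0.36 SD. A baseline difference at that limit moves the unadjusted end difference by r × 0.36 SD, which is 0.11, 0.18 or 0.25 SD for r = 0.3, 0.5 or 0.7.

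Given such an imbalance of k = 1.96 standard errors and no true effect, the chance of a significant unadjusted result is

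1 − Φ((1.96 − rk)/√(1 − r²)) + Φ((−1.96 − rk)/√(1 − r²)),

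which is 7.9%, 12.9% or 20.5%. Averaged over all randomisations it is 5%.

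**If fewer are analysed.** The sentence refers to a small subsample and does not say whether this means the 120 themselves or a part of them. The percentage reduction in variance does not depend on N; the equivalent patient numbers and the power do. With 30 per arm, for example, power for 0.5 SD is 49.1% without adjustment and 52.8%, 60.9% or 77.4% with it.

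**The case against.** The strongest reply is that this is one sentence in a condensed article. It does not say that the comparisons are separate or unadjusted, and it would also fit a comparison of change, a repeated-measures model, or a baseline-adjusted analysis with baseline values tabulated by arm. The choice of model and covariates is commonly left to the full protocol or the analysis plan, and neither is shown. This largely stands: the article cannot be said to have ruled out adjustment. What remains is that the sentence does state a form of analysis, its natural reading is a between-arm comparison at each time, and a later plan that follows it would inherit that form.

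A reader might go further and infer that the trial will claim an effect when the arms do not differ before and do differ after. That would be a poor inference, but no section states such a rule, and no significance test at baseline is mentioned. A reader might also infer that an unadjusted end comparison is invalid. It is not: between randomised arms it is unbiased over repeated randomisation and keeps its 5% type I error.

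Two further objections hold. The gain depends on a correlation that the article does not give and is modest at r = 0.3. And the existence of a pre-intervention measurement rests on the word *before* alone, because the Intervention group section lists only later assessments.

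**Conclusion.** The point holds as a free improvement. As described, the step 4 analysis includes a pre-treatment comparison that carries no information on the effect, and an end comparison that does not use the pre-intervention value. The cost is efficiency and exposure to chance imbalance in the one randomisation carried out; the validity of the end comparison is not in question. The 9% to 49% reduction in variance rests on the assumed range of r and on a continuous outcome; the equivalent sample sizes of 132 to 235 also require all 120 to be analysed. Confidence is moderate, because the form of the analysis is read from a single condensed sentence.

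**What to change.** Replace the step 4 analysis sentence with wording to this effect:

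*The treatment effect is the between-arm difference in the principal outcome at the end of the intervention, and at the assessment 3 months later, adjusted for the pre-intervention value of the same outcome by a model suited to its scale. Pre-intervention values will be described by arm and not tested.*

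The model type can be left open until the scale of the outcome is stated. The text gives no ground for requiring a linear model or a particular further covariate such as AUD severity. The Intervention group section should also list the pre-intervention assessment among the measurement times, so that the two sections agree.

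The cost is wording only, provided the outcome is measured before the sessions as *before* implies. If that was not intended, the cost is one added self-rating before the first session.

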## Discussion

This protocol is original because it applies marketing strategies to evaluate the impact of alcohol marketing on groups of drinkers with an AUD who are seeking treatment. There is no large body of data in literature which explores the influence of several types of marketing tools on drinkers with an AUD and uses a mixed methodology. However, this population of drinkers with an AUD does present a target for alcohol marketing strategies. Indeed drinkers presenting an AUD, represent 8% of the French population, but they represent 50% of alcohol purchases in France [49]. The ultimate objective is to be able to propose individual and collective prevention measures to help reduce the risk from alcohol toa vulnerable population of persons with an AUD. The expected impact of this project is multi-faceted. At a preventive level, this study will help to analyse the influence of alcohol marketing, and the modalities of this influence, on drinkers with an AUD who are seeking treatment. It will be one of the first large studies, using a mixed methodology, that will underline the probable impact of alcohol marketing on vulnerable drinkers with an AUD. These results will help to put pressure on public authorities to put in place preventive measures which could reduce the impact of marketing on patients with an AUD. Measures to be considered are: realistic and effective limits on advertising, in terms of the media used as well as the content, but which also take into consideration pricing and brand strategies.

These results would make it possible to discuss current collective prevention measures in France, including the regulation of alcohol marketing. The Evin law was introduced in 1991 [33], to limit exposure to advertisements for alcohol brands among the youngest members of society, with restrictions concerning certain marketing media (posters on the street, television, etc.) and the content of authorised advertising (informative and objective presentation of products...). However, it was gradually deconstructed, with the posting of advertisements being authorised in 1993; advertising on the Internet in 2009 [50]; and, more recently, (2015) an extension of the authorised media and advertising content, as long as the message referred to the gastronomic and cultural heritage and the geographical origin of the product [51]. The result of these developments is that exposure to advertising and marketing of alcohol brands has been growing in France in a significant way and we note their omnipresence in the daily environment of the citizens: posters in the street, promotions, competitions in shops, in the press, on the internet (official sites and social networks), radio and also in films and series etc. [20, 51]. Until now, public health actors failed to take a stand in favour of limiting these developments. Consumer protection is, however, a public duty and there are many public health issues at stake. Given the high social cost of alcohol use disorders, the results of this work seem particularly promising in reducing the societal financial impact of this disorder. With regard to the impact on public health, recommendations will be made to regulatory authorities to improve the supervision of advertising and, more broadly, alcohol marketing practices.

On atherapeutic level, this study will be innovative, with the development of counter-marketing messagesamong drinkers on an AUD program. This study will help to build the content of the educational intervention, including alcohol counter-marketing strategies. In addition, it will make it possible to identify whether this type of focusis useful in treating patients’craving and their perception of their ability to stop consuming alcohol. If this study shows that this kind of intervention improves outcomes for drinkers with an AUD, it will be necessary to develop strategies of this type for drinkers receiving AUD care. Alcohol use disorders are complex diseases:vulnerability factors are a combination of individual factors (gender, psychiatric disorders, familial history of addictive disorders..); environmental factors (social integration, social entertainment, professional and familial status..) and factors linked to alcohol (type of alcohol, social status, damage ..) Alcohol marketing interferes with the environmental factors, because it induces unconscious, daily exposure on multiple occasions, to alcohol marketing cues. It also interferes in factors linked to alcohol, because it maintains the status of alcohol, and positive social attitudes towards it, and it plays down the risks considerably. So in order to reduce the impact of marketing high-risk products,to these vulnerable patients, it would be invaluable to be able to show individuals how they are being affected by marketing without their knowledge, and to provide them with tools to resist such marketing. The hypothesis is that this intervention on demarketing, combined with a therapeutic educational program which targets strategies to control alcohol consumption, will help to give patients a better perception of control. It would help patients with an AUD to better resist alcohol advertising stimuli [40]. Such work has never been carried out in the field of alcohol use, nor on populations with problematic alcohol consumption.

## Data Availability

No complementary data available.

## Abbreviations

AUD: Alcohol use disorder
CBT: Cognitive Behavioural therapy
